Studies from the UK have shown a median time to remission of 9–12 months [9, 13, 14]. However, US studies report considerably shorter time to remission of 3–5 months [3, 10–12]. Studies from Brazil and Germany show remission times of 3–12 months and 3–6 months, respectively [15, 16]. Shorter treatment times could be related to reported differences in the relapse rates for CN, between 12 and 33% [13, 17–19], but without clear and consistent definitions for remission and relapse, this is unknown. There is also variation in the reported annual major amputation rates in people with CN from two different case series from hospitals in the USA—2.7% and 6.6% [20, 21].

The reasons for the variation are not understood but could include people’s characteristics at the start of the treatment, different techniques for monitoring CN, different protocols for the same monitoring techniques, variations in approach to off-loading and variability in study design. These could either underestimate or overestimate treatment duration.

Temperature difference between the feet is one of the most frequently used methods to monitor CN. It is recommended in the 2015 National Institute for Health and Care Excellence guidance on diabetic foot problems [22]. The most recent systematic review [8] published in 2013 recommends that immobilisation is continued until the temperature difference between the feet is less than 1–2 °C, and no further radiological changes on imaging have occurred. However, this recommendation is only based on level IV evidence, i.e. case series [8]. There is variability in the protocols used to measure the temperature difference between the feet. The most detailed protocol for measuring temperature discrepancy requires a 15-min acclimatisation period, controlled ambient air temperature and readings collected from nine different places on each foot [23]. In addition, plain X-rays demonstrate damage to the bone and joints rather than disease activity (inflammation).

Studies show inconsistency in the methods for monitoring and monitoring devices used [13, 17–19, 23–25]. These factors may overestimate or underestimate the degree of inflammation, so treatment may be discontinued too early or continued for longer than necessary. The presence of simultaneous bilateral foot disease or the absence of a contralateral limb through prior amputation invalidates the use of temperature measurement as a tool for identifying disease remission.

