### Outcomes

We will measure a range of feasibility, clinical efficacy and patient centred outcomes (Table 2). We will record time to MRI confirmed remission of CN with off-loading treatment (days), and its variance will be used to inform the sample size for a full-scale trial.

**Table 2 Tab2:** Feasibility, clinical efficacy and patient centred outcomes

Feasibility outcomes	Clinical efficacy outcomes (collected at all study visit)	Patient centred outcomes (collected at baseline, 3 monthly until remission, then at 1 and 6 months post remission)
The proportion of patients who meet the eligibility criteria	Number of new ulcerations on the index or contralateral foot	Health-related quality of life measured: Short Form 12 questionnaire (SF-12) [40] EuroQol-5D-5 L questionnaire (EQ-5D-5 L) [41]
The number of eligible patients recruited	Number of new infections on the index or contralateral foot	Hospital Anxiety and Depression Scale (HADS) [42]
The number of participants in which an alternative diagnosis is made during the active phase of the trial	Number of minor and major amputations on the index or contralateral foot at the end of the follow-up phase of the study	Pain as assessed by Visual Analogue Scale (VAS)
The proportion of patients that withdraw or are lost to follow-up. The term ‘withdrawal’ encompasses two potential scenarios: withdrawal due to loss of consent or withdrawal due to deaths	Number and severity of falls (Hopkins Fall Grading System) [43]	Patient diary
Statistical parameters of the key outcome measures, duration in off-loading to inform a sample size calculation for a definitive trial	The number of participants in each arm requiring further intervention for CN (e.g. further immobilisation) within 6 months of remission	
Ability to collect quality of life and resource use data		

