### Analyses

#### Quantitative analysis

The feasibility measures including eligibility, recruitment, retention and withdrawals will be reported as point estimates with 95% confidence intervals. There is no intention to conduct any formal comparative analyses for these measures, though levels of missing data will be explored with respect to certain baseline characteristics, e.g. age and measures of disease severity. Variability in outcomes (e.g. standard deviation) will be estimated with 95% confidence intervals to inform the sample size calculations for a full-scale trial. Any between-group efficacy analyses will only be exploratory. There are no plans for any interim analyses.

We will assess progression of foot deformity by comparing X-rays at baseline, remission and six months post remission. We will measure the change in the calcaneal inclination, talar declination and talo-first metatarsal angle between the X-rays. People who have undergone previous minor amputation and/or previous orthopaedic surgical fixation of the foot which alters or removes the anatomical landmarks of the foot will be excluded from this analysis due to the absence of bony landmarks.

The main purpose of the economic analysis is to inform how the data on costs and effects would be collected within a definitive study. Thus, we will estimate completion rates and seek to identify big cost drivers, in order to inform this decision. A preliminary cost-effectiveness analysis will also be performed, although the findings will be treated with caution. As such, we will estimate the mean incremental cost and mean QALY gain associated with the intervention compared to standard care plus.

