#### Safety reporting

Safety monitoring and reporting of adverse events has been discussed and agreed with the sponsor. The study has been assessed as low risk; therefore, there will not be a data monitoring committee. The intervention consists of increased frequency of MRI scans without contrast, so a pragmatic approach to safety reporting will be used. MRI scans will be performed in NHS hospitals under routine clinical protocols. Adverse events resulting from MRI scans will be reported by the research teams in line with the Hospital Trust’s clinical incident reporting policy. A copy of the anonymised incident form will be forwarded to the Chief Investigator (CG) and reviewed by the Trial Management Group. All other anticipated events, e.g. ulceration, infection, amputation, pain, falls and death will be recorded as secondary outcomes.

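### The X-ray deformity analysis excludes whole people for lost landmarks, where only the affected angle need be dropped

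*Protocol article*

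**What the plan says.** The rule is in the protocol article under Analyses, Quantitative analysis. The comparison is set out first: "We will assess progression of foot deformity by comparing X-rays at baseline, remission and six months post remission". The measures follow: "We will measure the change in the calcaneal inclination, talar declination and talo-first metatarsal angle between the X-rays". The exclusion is then stated for "People who have undergone previous minor amputation and/or previous orthopaedic surgical fixation of the foot which alters or removes the anatomical landmarks of the foot", and such people "will be excluded from this analysis due to the absence of bony landmarks".

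The eligibility criteria do not keep these people out of the trial. Table 1 excludes a previous major amputation on the opposite side, but not a previous minor amputation or fixation of the index foot. The Participants section also names a history of foot complications as something to vary in the qualitative sample, so the trial expects to enrol some people with one.

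Amputation during the trial is counted elsewhere. Table 2 lists "Number of minor and major amputations on the index or contralateral foot at the end of the follow-up phase of the study", and Safety reporting adds: "All other anticipated events, e.g. ulceration, infection, amputation, pain, falls and death will be recorded as secondary outcomes".

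**The concern.** The unit of measurement is the angle and the unit of exclusion is the person. By their names the three angles do not all involve the same bones: only the third names the first metatarsal. Surgery that removed the landmark for one angle may leave another measurable, yet the rule as written gives up all three. Its trigger is also wider than its reason. It covers landmarks that were altered as well as those removed, but is justified only by their absence.

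Deformity progression matters here because the trial explores whether immobilisation can be shortened, and the Background names keeping the foot's architecture as a treatment aim. The trial also asks whether clinical measures can feasibly be collected. How often each angle can be measured is part of that answer, and exclusion by person hides it. What is at stake is wider intervals, and results that leave out people with earlier foot surgery even where they have usable data.

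**Working it through.** **1. The text side by side.**
- Measured: change in three angles, each separately.
- Excluded: people, from the analysis as a whole.
- Reason: missing landmarks.
- Not stated: which landmarks each angle needs, or whether losing one is enough. Surgery that left the landmarks intact excludes nobody.

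Following the stated reason angle by angle would drop only angles that cannot be read. The rule as written can also drop readable ones.

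**2. The plan's own figure.** The article gives no number for the X-ray analysis. Its only planning figure is 60 participants, with an allowance of 10–15% for alternative diagnoses. As a consistency check, the upper end of the cited range gives 50 / (1 − 0.15) = 58.8, or 59, close to 60. That figure is not in dispute. After the allowance the evaluable number is 60 × 0.85 = 51 to 60 × 0.90 = 54.

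**3. Cost of exclusion by person.** Let *f* be the share of evaluable people excluded for earlier surgery. The article gives no value, so *f* is assumed and shown over a range. Suppose also that the other two angles are measurable in everyone excluded, and that the spread of change is the same in them as in the rest. The standard error for such an angle then grows by √(1 / (1 − *f*)). Taking 51 people:

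| *f* (assumed) | people removed | people left | SE ratio | person-angles recoverable (2 per person) |
|---|---|---|---|---|
| 5% | 2.55 | 48.45 | 1.026 | 5.1 |
| 10% | 5.1 | 45.9 | 1.054 | 10.2 |
| 20% | 10.2 | 40.8 | 1.118 | 20.4 |
| 30% | 15.3 | 35.7 | 1.195 | 30.6 |

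Starting from 54 people, 10–20% removes 5.4 to 10.8; the ratios do not change, because they depend only on *f*. Interval width follows the standard error closely, so 10–20% excluded means intervals about 5–12% wider than needed.

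**4. If fewer angles can be recovered.** Let *g* be the share of excluded people in whom a given angle is measurable. The ratio becomes √((1 − *f*(1 − *g*)) / (1 − *f*)). With *g* = 0.5 (assumed):
- *f* = 10%: √(0.95 / 0.90) = 1.027.
- *f* = 20%: √(0.90 / 0.80) = 1.061.

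The cost is then about 3–6%.

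**5. Bias between arms.** If *previous* means before the baseline film, exclusion depends on something fixed at entry. It shrinks and narrows the analysis set but does not select on what happens under the allocated monitoring. The article does not define the word. If it also took in surgery between films, exclusion would depend on events after randomisation, which is why a short definition is worth adding.

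**The case against.** The strongest reply is that the rule is defensible and the stakes are low. The article does not define the reference lines, so it cannot be shown from the text that two of three angles usually survive. A previously fixed segment may also change little, which is a reason to leave it out. The study has no power calculation, between-group efficacy analyses are exploratory, and the angles are not among the Table 2 outcomes. All of this stands, and it limits the size of the point. It does not defend dropping an angle whose landmarks are intact. The fix does not rely on any particular mapping of angles to bones, and it leaves room to drop an altered landmark that is judged unusable.

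A reader might infer something stronger: that feet amputated or fixed during the trial drop out or look corrected, that progression is therefore understated, and that differences between arms in severe outcomes are hidden. The documents do not support this. The article is silent on surgery between films, and a condensed article may leave such handling to the full protocol or analysis plan. Amputations are an outcome in their own right, and Table 2 also counts, by arm, people needing more treatment for Charcot neuroarthropathy in the six months after remission. Nor do the Background's annual major amputation rates (2.7% and 6.6%) measure harm from this rule, since a foot lost to major amputation has no later angle under any wording.

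**Conclusion.** The point holds as a narrow one. The article states a person-level exclusion for an analysis of three separate angles, and its own reason supports an angle-level exclusion. The likely cost is intervals about 5–12% wider than needed for angles that remain measurable, together with reduced generalisability to people with earlier foot surgery. That size rests on three assumptions: 10–20% of about 51 evaluable people are excluded, their other angles can be read, and the spread of change is similar in them. With only half of those angles readable, the cost is about 3–6%. No stated number is wrong. If *previous* refers to surgery before the baseline film, the rule does not bias the arm comparison. This is a cheap improvement to an exploratory measure and does not threaten the trial's main aims.

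**What to change.** In the Quantitative analysis section, replace exclusion of people with exclusion of angles. Omit an angle only when the landmarks for that angle are absent or unusable at baseline, keep the participant's other angles, and report the number analysed for each angle.

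As a minor addition, state that *previous* means before the baseline film. Beside the angle results, list by arm any participants whose index foot was amputated or surgically fixed between films, so that a surgically changed angle is not read as a change in deformity.

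The cost is a sentence or two of text and a short listing. The three angles will have slightly different denominators. No new films or readers are needed.

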#### Qualitative analysis

The qualitative interviews will be analysed using inductive thematic analysis using the six-step model [47]. The first author (CG) will read all the transcribed interviews to record emerging ideas. The interviews will then be subjected to line-by-line coding using the NVivo data management package. The coding framework will be refined by a second researcher, who will cross-check it against a small sample of transcripts. A modified framework approach will be used to organise the analysis. The coded data will be subjected to a thematic analysis, identifying key categories and themes from the data, ensuring that all participants’ responses are adequately captured and their meaning authentically interpreted. This approach will provide rich descriptions of the data representing accounts of the diverse and personal experiences of people who have taken part in the study and been treated for acute CN.

#### Data management and quality assurance

We will set up a Trial Management Group to assist with co-ordination and strategic management of the feasibility study. An initial on-site initiation visit will be completed by CG prior to the sites opening. The primary method of data collection by the research teams will be direct online entry of data onto a purpose-designed secure password-protected electronic case record form. The database complies with data protection requirements [48] on confidentiality and anonymity. Quality management and monitoring procedures have been discussed and agreed with the sponsor. Central monitoring has been considered appropriate for this study with the option to escalate findings and conduct ‘for-cause’ on-site triggered monitoring visit if indicated. We will review completed consent forms and selected data points for quality assurance at each site within a week after randomisation of the first participant. Subsequent monitoring will be completed at six monthly intervals to coincide with the Trial Management Group meetings and at the end of data collection.

#### Safety reporting

Safety monitoring and reporting of adverse events has been discussed and agreed with the sponsor. The study has been assessed as low risk; therefore, there will not be a data monitoring committee. The intervention consists of increased frequency of MRI scans without contrast, so a pragmatic approach to safety reporting will be used. MRI scans will be performed in NHS hospitals under routine clinical protocols. Adverse events resulting from MRI scans will be reported by the research teams in line with the Hospital Trust’s clinical incident reporting policy. A copy of the anonymised incident form will be forwarded to the Chief Investigator (CG) and reviewed by the Trial Management Group. All other anticipated events, e.g. ulceration, infection, amputation, pain, falls and death will be recorded as secondary outcomes.

## Discussion

CN is a poorly understood and under researched complication of diabetes, associated with increased morbidity and mortality compared to people with diabetes without peripheral neuropathy. Evidence is lacking about the factors that influence the unexplained variation in treatment times, relapse rates and complications such as ulceration and amputation. We have also identified a lack of evidence to support the efficacy of current monitoring techniques in CN. There is evidence from small studies that MRI may be superior to current methods of monitoring for remission in CN, but this has not been formally evaluated using robust designs. The results of this feasibility study will inform the decision about progressing to a full-sized pragmatic randomised controlled trial: the number of sites required, trial design, the frequency of MRI monitoring and the choice of process and outcome measures. The embedded qualitative study will provide contextual and meaningful insight into people’s experiences of living with CN and what factors they see as contributing to their engagement with the prescribed treatment. Secondly, the qualitative study will advance our understanding of how the condition impacts on participants’ quality of life and may contribute to future work on patient reported outcomes measures in this area [49]. Finally, the findings from the qualitative study will provide additional insights into aspects of the trial design and processes that could be improved, in terms of engagement of, and acceptability to participants, based on the participants’ experience of involvement in the feasibility study. These aspects could include feedback on the frequency of trial visits, the length of the active and follow-up phases of the trial and the choice and frequency of completing validated questionnaires. The results of this study will be disseminated to researchers, clinicians, people with diabetes and relevant stakeholders through presentations, publications and social media press releases.

### Trial status

The CADOM trial originally opened for recruitment in December 2017 and is currently recruiting participants. Recruitment will continue until the end of November 2019.

## Data Availability

The datasets generated and/or analysed during the current trial will be available from the corresponding author on reasonable request, provided appropriate credit is attributed to the original authors and the data source.

## Abbreviations

ABPI: Ankle brachial pressure index
BMI: Body mass index
CN: Charcot neuroarthropathy
eGFR: Estimated Glomerular filtration rate, ml/min
EQ-5D-5 L: Euroqol 5D
F: Follow-up visit
HADS: Hospital Anxiety and Depression Scale
HbA1c: Glycated haemoglobin (A1c), mmol/mol
MRI: Magnetic resonance imaging
NHS: National Health Service
R: Remission
SF-12: Medical Outcomes Short-Form Health Questionnaire
VAS: Visual Analogue Scale
